## Methods: monitoring

We have appointed an independent steering committee comprising three members: a climate change and health domain expert, a clinical trials expert, and a biostatistician to maintain project oversight throughout the study. The steering committee will convene three meetings, the last of which will be in June 2023. At these meetings, the research team will review the conduct of the trial, including a review of adherence to intervention components, logistical issues, and completeness and quality of collected data. Our biostatisticians will also present emerging effect estimates in the intervention and control arms to the steering committee, who will ascertain whether the results display:Null finding(s) > indicating the study should stopSignificant finding(s) > indicating the study should stopEmerging positive finding(s), but statistically insignificant > indicating the study should potentially continue, and therefore, the data collection should continue for a recommended duration.

The cool roof is a passive home cooling intervention and, therefore, required no human interaction or behavior change on behalf of our participants. We conducted an education program through our field staff to ensure study participants did not place items on their roofs that could obstruct the optimal performance of the cool roof. Our field teams regularly monitored roofs during monthly home visits and highlighted any deterioration or other issues for resolution. Throughout the trial, our study team exchanged regular communication via virtual and phone calls, emails, and short messages about trial progress.

We encountered, however, adherence issues with participants removing smartwatches, particularly at night. Our field team explained the importance of smartwatch data and encouraged non-compliant individuals to wear the device during home visits.

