**Methods:**

We are conducting a 2-year community-based stratified cluster randomized controlled trial (cRCT) implementing sunlight-reflecting roof coatings, known as “cool roofs,” as a climate change adaptation intervention for passive indoor home cooling. Our primary research objective is to investigate the effects of cool roofs on health, indoor climate, economic, and behavioral outcomes in rural Burkina Faso. This cRCT is nested in the Nouna Health and Demographic Surveillance System (HDSS), a population-based dynamic cohort study of all people living in a geographically contiguous area covering 59 villages, 14305 households and 28610 individuals. We recruited 1200 participants, one woman and one man, each in 600 households in 25 villages in the Nouna HDSS. We stratified our sample by (i) village and (ii) two prevalent roof types in this area of Burkina Faso: mud brick and tin. We randomized the same number of people (12) and homes (6) in each stratum 1:1 to receiving vs. not receiving the cool roof. We are collecting outcome data on one primary endpoint - heart rate, (a measure of heat stress) and 22 secondary outcomes encompassing indoor climate parameters, blood pressure, body temperature, heat-related outcomes, blood glucose, sleep, cognition, mental health, health facility utilization, economic and productivity outcomes, mosquito count, life satisfaction, gender-based violence, and food consumption. We followed all participants for 2 years, conducting monthly home visits to collect objective and subjective outcomes. Approximately 12% of participants (*n* = 152) used smartwatches to continuously measure endpoints including heart rate, sleep and activity.

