### Power calculations

Prior non-randomized studies indicate that reducing the indoor temperature by 3–4 °C should decrease heart rate by several beats per minute [32, 50, 51]. Because of high uncertainty about the previous findings, their attributability to the climate and context in rural Burkina Faso, and the relatively large number of secondary endpoints, our cRCT is powered conservatively (Table 3). In the baseline power calculation, the minimal detectable heart rate difference between the cool roof intervention and control condition arm is 0.22 beats per minute (Table 3) for 300 homes (in the intent to treat) in both arms, assuming a significance level of 5% and power of 80%. We further assumed that 15% of homes refuse to participate in the trial and 15% of individuals would be lost to follow-up. Our sensitivity analyses showed that these power calculation results are highly robust to changes in intra-cluster correlation, the number of individuals in which the outcomes were measured per home, and the base correlation generated by our stratification (Table 3).

**Table 3 Tab3:** Minimal detectable difference in heart rate — baseline power calculation and sensitivity analyses

No. individuals/baseline correlation	1	2	3
ICC = 0.1			
0	0.28	0.21	0.18
0.1	0.28	0.21	0.18
0.2	0.28	0.20	0.17
ICC = 0.2			
0	0.28	**0.22**	0.19
0.1	0.28	0.22	0.19
0.2	0.28	0.21	0.19
ICC = 0.3			
0	0.28	0.23	0.21
0.1	0.28	0.23	0.20
0.2	0.28	0.22	0.20

The significance level is 0.05

The table shows the minimal detectable differences in heart rate (in beats per minute) for 300 homes in each arm for a range of combinations of values of the intracluster correlation coefficient (ICC), the number of individuals per home, and the baseline correlation generated by our stratification

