### Statistical analysis

#### Analysis of monthly home visit data

The analysis for our primary outcome, heart rate, will be performed on the principle of intention-to-treat (ITT). We will use generalized linear mixed models (GLMM) to analyze the causal effect of cool roofs on our primary and secondary endpoints. In addition to the base-case estimations, without covariate controls, we will also estimate the intervention effect of cool roofs by adjusting for covariates to boost statistical efficiency. We will adjust for clustering of standard errors at the household level.

To estimate the intervention effect of cool roofs on heart rate, we will report the effect estimates comparing intervention and control arms based on the hypothesis that effects will be greatest during the hottest month of the year (April). We will additionally report effect estimates at monthly intervals of data collection, except for HbA1c (which is measured in two time points), because we hypothesize the intervention effect will vary based on outdoor weather conditions during the trial period; therefore, we will include an interaction term between the intervention and the month of trial. We will perform additional sub-analysis by selected variables where relevant (i.e., by season, gender, age group, time of the day (day/night), and roof type). We will explore the use of different imputation methods for missing values in the covariates. We will conduct sensitivity analysis, including repeating analyses accounting for individuals lost to follow-up. All data analyses will be performed using R software.

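### The monitoring rule points to stopping on significant or null findings and to extending on near-misses, over three meetings, with no endpoint named and 5% the only level given; at 0.05 per look the overall error is about 7–12%

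*Protocol article*

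**What the plan says.** All references are to the protocol article.

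- **Number of looks** (Methods: monitoring): "The steering committee will convene three meetings, the last of which will be in June 2023". The dates of the first two are not given.
- **What is shown** (same section): "Our biostatisticians will also present emerging effect estimates in the intervention and control arms to the steering committee".
- **The rule** (same section): the committee decides whether results "display:Null finding(s) > indicating the study should stopSignificant finding(s) > indicating the study should stopEmerging positive finding(s), but statistically insignificant". Null and significant findings each indicate a stop. A positive but non-significant result indicates that the study should potentially go on and that "the data collection should continue for a recommended duration". No cap on that duration is given.
- **Scope of a finding** (abstract, Methods): "We are collecting outcome data on one primary endpoint - heart rate, (a measure of heat stress) and 22 secondary outcomes". The monitoring section does not limit findings to the primary endpoint.
- **Significance level** (Power calculations): the detectable difference is derived "assuming a significance level of 5% and power of 80"%. No other level appears in the article.
- **Timing of the effect** (Analysis of monthly home visit data): the heart-rate comparison rests on the hypothesis that "effects will be greatest during the hottest month of the year (April"), and the effect is expected to vary with the weather.
- **Calendar** (Timeline; Trial status): roofs were coated from April 23 to June 4, 2021, and data collection ended on June 30, 2023.

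**The concern.** Three features of the rule combine badly.

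1. **The amount of data depends on the p-value.** Stopping once a result is significant, and collecting more when it is positive but short of significance, gives the trial several chances to cross the same threshold. The final p-value and confidence interval then lose their nominal meaning unless the threshold is adjusted.
2. **Two opposite actions share one undefined region.** Null and positive-but-insignificant results are both non-significant. One points to stopping and the other to extending, and no dividing line is stated.
3. **A null stop is not tied to the season that matters.** The coating dates leave only April 2022 and April 2023 as complete Aprils under treatment. The rule would allow a null stop before either, although the effect is expected to be largest then.

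At stake are the type I error of the primary conclusion and the chance of ending data collection before the most informative month has been observed.

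**Working it through.** **Inputs from the article.** Level 5%, taken as two-sided because sidedness is not stated; power 80%; three meetings. The 0.22 beats-per-minute detectable difference does not enter, because the calculation works on the z scale.

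**Assumptions.** 0.05 is applied at every look; one endpoint; z-statistics follow the usual group-sequential process, with z at information fraction t distributed as N(δ√t, 1). Spacing is varied because the dates are not given.

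**Starting point.** One look at |z|>1.96 gives 5.0%, the article's stated level.

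**Step 1: overall error without a null stop.** P(|z|>1.96 at any look) under no effect, by simulation with 2 million paths per scenario:

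| Looks (information fractions) | Overall error |
|---|---|
| 2, equally spaced | 8.3% |
| 3, at 0.8, 0.9, 1 | 7.8% |
| 3, at 0.5, 0.75, 1 | 9.7% |
| 3, equally spaced | 10.7% |
| 3, at 0.1, 0.5, 1 | 12.3% |
| 4, equally spaced (one extension after June 2023) | 12.6% |

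**Step 2: credit the null stop.** If a null result ends the study at looks 1 and 2, some paths that would later have crossed 1.96 are removed. With three equal looks:

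- null defined as z<0: 7.8%
- null defined as z<0.5: 7.4%
- null defined as z<0.674: 7.2%

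All three cut-offs are illustrative. Over Steps 1 and 2, three looks give about 7–12%.

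**Step 3: more than one endpoint.** With 1 + 22 = 23 endpoints, a single look at 0.05 each gives 1 − 0.95^23 = 69% if the endpoints were independent. They are not, so this is only an indication of direction: letting any endpoint count raises the error above the one-endpoint figures.

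**Step 4: risk of a null stop when the intervention works.** For 80% power at a two-sided 5% level, δ = 1.960 + 0.842 = 2.802. At one-third of the information with a constant effect, the mean of z is 2.802 × √(1/3) = 1.617. Then P(z<0.5) = Φ(0.5 − 1.617) = Φ(−1.117) = 13%. Over looks 1 and 2 together, the chance of a null stop is 5.7% for z<0 and 18.6% for z<0.674.

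**Step 5: adjusted boundaries.**

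- Haybittle–Peto: p<0.001 means |z|>3.29 at the two earlier meetings. A final critical value of about 1.965 then holds 5.0% overall with equal spacing.
- O'Brien–Fleming with equal spacing: |z| of 3.47, 2.45 and 2.00 gives 5.0% overall.
- Power of the final test alone at δ = 2.802: Φ(2.802 − 1.965) = Φ(0.837) = 79.9%, and Φ(2.802 − 2.004) = Φ(0.798) = 78.7%, against 80% at 1.96.

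**The case against.** The strongest reply is that the article does not say the looks are unadjusted. The 5% belongs to the power calculation. Interim boundaries and futility cut-offs are commonly kept in an analysis plan or committee charter, and neither is shown. The wording is advisory, and the committee is independent and includes a biostatistician and a clinical trials expert. Data collection ran to June 30, 2023, so both treated Aprils were covered.

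Much of this stands, and it rules out several stronger readings that a reader might infer:

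- *That the trial had to stop at any significant result.* The text says what findings indicate; it does not bind the committee.
- *That the error rate is doubled.* This is near the upper part of the range. It needs 0.05 at each look, roughly equal or early spacing, and a null stop that is not binding. With a binding one-sided null stop the figure is 7.2–7.8%.
- *That a look before April would be null.* With zero effect, z<0.5 occurs Φ(0.5) = 69% of the time. But the article says the effect is greatest in April, not absent at other times, and neither earlier meeting is dated. Its Table 1 gives a median daily maximum of 36.4 °C, so heat is not confined to April.
- *That a working intervention would be withdrawn.* The coating was applied once in 2021. Only the study and its data collection could stop.
- *That the trial stopped early or lost a hot season.* Nothing in the article shows this. The June 2023 meeting falls in the last month of data collection, so only the first two could have led to an early stop.

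The reply does not remove the point. The article does not leave the decision rule to another document. It states one, in terms of significance and an undefined null, and the only level beside it is 5%. A boundary kept elsewhere would have to replace that wording.

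**Conclusion.** The point holds as a rule that is badly fixed in the text. Followed as written with 0.05 at each look, it gives an overall two-sided error of about 7–12% for one endpoint against a stated 5%. The value depends on look spacing and on whether a null result binds, and neither is given. Every three-look scenario examined exceeds 5%. A further look after an extension, or decisions based on secondary endpoints, would add to it.

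Separately, null and positive-but-insignificant are not distinguished, and a null stop before a complete treated April is allowed. With a constant effect at 80% power and an illustrative cut-off of z<0.5, a look at one-third of the information would read as null 13% of the time.

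The concern is with the stated rule and with how the final test is interpreted. No early stop or actual error is shown.

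**What to change.** Replace the three indications in Methods: monitoring, and carry the change into the analysis plan:

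1. **Endpoint.** Base any decision to stop or extend on the primary heart-rate contrast only. Secondary findings trigger neither.
2. **Significance.** Use p<0.001 (|z|>3.29) at the two earlier meetings and a final critical value of about 1.965. Alternatively, use an O'Brien–Fleming-type spending function evaluated at the actual information, which gives 3.47, 2.45 and 2.00 if the looks are equally spaced.
3. **Null.** Give a numerical futility criterion that separates null from positive but non-significant, and require at least one complete post-coating April before a null stop.

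Since data collection has ended, the part that still bears on the results is disclosure. Report when the two earlier meetings took place, what was shown and decided, and whether data collection was extended. Judge the final primary test against the adjusted critical value.

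The cost is a change of wording and a final critical value slightly above 1.96. Power of the final test falls from 80% to about 79.9% (Haybittle–Peto) or 78.7% (O'Brien–Fleming), before counting rejections at the earlier looks.

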## Ethics and dissemination

### Research ethics approval

Our study protocol was approved by the Ethics Committee of the Medical Faculty of the University of Heidelberg on May 6, 2019 (S-293/2019) prior to the trial commencing. We registered the trial and study design with all primary and secondary endpoints and analytical approaches as trial DRKS00023207 in the German Clinical Trials Register (DRKS) (https://www.drks.de/drks_web/).

Our co-investigators are formally trained in research ethics through the US Collaborative Institutional Training Initiative (CITI). The co-investigators trained the data collection teams on research ethics. We guided our data collection team on facets of research ethics including principles of respect for persons (including autonomy, which includes the right for individuals to decline or withdraw from our trial, and the protection of vulnerable subjects), beneficence (the importance that we do no harm), and justice (in terms of the distribution of information and the inclusion of participants).

### Plans for communicating important protocol amendments to relevant parties

The Ethics Commission of the Medical Faculty of the University of Heidelberg was contacted and notified about any protocol amendments requiring their acceptance. Following the approval of the Ethics Committee and before implementation, all research members were informed about protocol amendments.

### Consent and withdrawal

Our trial will adhere to the principles outlined in the Declaration of Helsinki and the Belmont Report, which prioritize respect for persons, beneficence, and justice. We provided written study information and the informed consent form to eligible individuals. The study manager explained the study's aims and detailed procedures — in the presence of a witness if required. We provided sufficient time for our participants given to the subject to decide whether or not to participate in the study. Participants were given the opportunity to enquire about details of the study and any questions regarding the study, and responses were provided. For illiterate participants, we obtained a thumbprint signing and a witness’ signature to document consent before enrolment. We requested consent to collect blood samples to analyze the blood samples and any biological material. We obtained written, informed consent to participate from all participants.

Our trial participants were informed that consent can be withdrawn at any point in time, including the destruction of biological samples and deletion of collected data, without bearing any negative effects in terms of health care or otherwise. We will inform our trial participants about abnormal results emerging from data collection and refer them to the health center for further investigation and treatment. Enrolment of participants in the study will, therefore, ensure adequate treatment is initiated if there are any indications. Participants in our trial will not have to relinquish any concomitant care. We anticipate no direct harm as cool roof products applied to roofs have met regulatory safety standards and are not in direct contact with participants. We will repair any damage to the cool roof coatings during the course of the study.

We informed eligible households about the risks and benefits of participation in our trial. None of the participants received any direct compensation for their participation. Homeowners were, however, given €11.45 for raw material costs to fix damaged mud brick roofs or coat them with shea butter as was the custom following the rainy season. Every participant is free to refuse or interrupt data collection at any point in time. A decision not to participate in this study will not bear any further consequences for the individual. We explained that participation in our current trial can potentially generate the benefit of a cooler house, which can lead to health benefits for participants as a result of their participation. There will be no special criteria for discontinuing or modifying the allocated interventions. We will, however, track reasons for attrition and report these in subsequent publications.

After study completion, we will provide relatable summaries of study results to acknowledge participants' contributions. Furthermore, we will provide our scientific findings to participants in an engagement workshop for community leaders, participants in the focus groups, and those involved in prognostication and co-production of interventions for further studies related to cool roofs. We anticipate that this feedback will be valuable to some participants because it will provide them with insights that can support future cool roofing initiatives. Regarding post-trial care, there is no anticipated harm and compensation for trial participation - study participants in the control arm will be offered a cool roof at the end of the trial, if we find positive effects.

No invasive procedures are to be borne by study participants other than those involved in routine diagnostic procedures, and no procedures other than those outlined here will be performed.

### Confidentiality

Complete confidentiality of data will apply, and the data collection will conform to requirements of the national and federal legislations on data protection. We are storing digital data on password-protected files. Data is available exclusively to the research team members for complete confidentiality. Third parties will receive anonymized data only for research purposes. Informed consent forms, laboratory books, and other participant-related documents will be safely stored during study conduct and, subsequently, at the Co-Principal Investigator’s office premises.

### Dissemination

Upon completion of the study, participant-related information on results will be provided to the families and exclusively by the clinical officer in charge or the Principal Investigator. Results will also be presented at international peer-reviewed journals, national and international conferences (ranging from academic conferences to United Nations Climate Change Conference (COP) meetings), our project website, and through media publications and interviews [54].

## Discussion and policy implications

Our cRCT described here tests whether a passive home cooling technology — cool roofs — reduces indoor ambient temperature and improves cardiovascular, metabolic, sleep, mental health, and general health outcomes in Nouna, Burkina Faso- a region highly vulnerable to increasing heat exposure from climate change. When applied to homes as described in this study, cool roofs may serve as a feasible and scalable intervention for adapting to and ameliorating the effects of extreme heat. The impact, in practice, depends on the uptake. Cool roofs are attractive as a passive, inexpensive technology that does not require behavior change and carries desirable co-benefits such as roof waterproofing and indoor noise reduction. Our trial is an interdisciplinary project bringing together elements of public health, medicine, occupational health, engineering, materials science, development, and public policy. We linked social science and epidemiology to develop the trial design; engineering and material science to understand building design and heat transfer; natural science and occupational health to define endpoints and understand heat effects on health and productivity; and development and public policy to engage decision-makers and donors.

The most important facet for intervention uptake is community buy-in, which stems from our participatory research model — where we are actively engaging and partnering with local stakeholders and community members. Through this partnership model, we are gaining an understanding of community adaptation needs to reduce adverse health effects of heat exposure. We designed all project activities to give Nouna community members a sense of agency, control, and empowerment. We trained and employed local painters to apply the cool roof coating successfully. We planned the logistics of coating procurement, storage, distribution, application, and maintenance (in case of damages) to ensure the coating application was finalized in a short window between COVID-19 field work restrictions ending and the commencement of the rainy season. Participants were compensated for materials to repair roof damages following the rainy season. We trained local interviewers for monthly home visits, and local field staff were also trained exclusively in retrieving smartwatch data. Two local entomological field teams were also responsible for collecting mosquito specimens. The intervention was introduced through focus group discussions, community leader interactions, and home visits, often using cool roof samples to showcase the technology. We created a 5-min video of our cool roof adaptation trial to engage a broader audience [55].

Adaptation is necessary to reduce the harm caused by climate change, but adaptative capabilities are distributed inequitably, and resource-constrained regions are often those least able to adapt [56, 57]. Despite the need to test and deploy adaptation interventions in Africa, current initiatives are insufficient. Complex field trials on climate change adaptation rarely prioritize the most vulnerable populations, such as those in Nouna, Burkina Faso. Yet, this is where trials are most needed [58]. Between 1991 and 2021, the average surface temperature over the African continent has risen 0.3 °C per decade faster than the global average, and the frequency of extremely hot days also has increased [59]. Projections indicate these trends will continue into the future — leading to adverse health effects [60]. Furthermore, there may be devastating effects on populations due to disrupted agriculture/food security, conflict, and displacement [61–63]. In response, more than 40 African nations have committed to more ambitious adaptation efforts in their national adaptation plans (NAPs), and the cool roofs project in Nouna demonstrates it is possible to conduct field trials in a region facing climate, security, and political challenges.

Strengthening local capacity and bolstering NAPs requires improving pathways for the transfer of low-carbon technology to regions like Nouna. As with potentially desirable low-carbon technologies, cool roof coatings are not currently manufactured locally in Burkina Faso. In our trial, we have successfully engaged with a European non-governmental organization — the European Cool Roof Council (ECRC) — that has the mandate to promote the use and expansion of low-carbon technology, such as cool roofs, in the European Union. Three ECRC member companies — Sika AG, Engineered Polymer Solutions B.V., and SOPREMA SAS — expressed interest in sponsoring cool roof coatings for our trial free of charge (as unrestricted educational grants). Our engagement is the first step in building awareness of the need for low-carbon technologies such as cool roofs in Africa, and it highlights the importance of developing public–private partnerships for embedding low-carbon technology solutions in local African environments.

In addition to involving local communities and industry, we must engage policymakers. In New Zealand, RCTs investigating the impact of installing insulation or non-polluting home heating on respiratory outcomes were instrumental in creating a government subsidy scheme for low-income households to receive insulation and heating grants [64–66]. These studies demonstrated the power of intervention research, providing robust evidence for governments to formulate effective policies. Considering the deficiency of local empirical trials on housing adaptation and health in climate-vulnerable African regions, our study will be integral in shaping policy development in this region [67]. To ensure the policy relevance of our research, we have engaged the Director General of the National Institute of Public Health in Burkina Faso to drive collective responses to observed impacts and provide resources to facilitate adaptation and manage access to resources [67]. Since establishing the trial, we have engaged government agencies in Burkina Faso, including the Ministry of Health and the Ministry of Aviation and Transport. We will further engage the Ministry of Environment, Green Economy, and Climate Change of Burkina Faso. Our trial has also been featured in the Global Heat Health Information Network (GHHIN) monthly digest and at the 2021 United Nations Climate Change Conference (COP26) event on climate change adaptation in Africa.

Sociodemographic structure, local economic forces, and community values are driving forces mediating adaptive capacity to climate change, especially in Burkina Faso [68, 69]. These factors highlight the need for simple interventions, such as cool roofs that improve adaptive capacity uniformly across populations. Though inexpensive technologies for climate change adaptation exist research on the effects of these interventions in resource-constrained regions of the globe is limited. Even less well-studied are the downstream improvements these interventions can have on health. Evidence demonstrating the effectiveness of adaptation interventions such as cool roofs is critical for policymakers with limited budgets who must rely on proven technologies for health improvements. Our trial bridges this gap and provides causal, policy-relevant empirical evidence for the potential inclusion of cool roofs in adaptation policy packages in low-resource settings vulnerable to climate change.

